## Abstract

**Background:**

One of the major risk variables for surgical site infection is wound management. Understanding infection risk factors for breast operations is essential in order to develop infection-prevention strategies and improve surgical outcomes. The aim of this trial is to assess the influence of dressing wear time on surgical site infection rates and skin colonization. Patients’ perception at self-assessment will also be analyzed.

**Methods/Design:**

This is a two-arm randomized controlled trial. Two hundred breast cancer patients undergoing immediate or delayed breast reconstruction will be prospectively enrolled. Patients will be randomly allocated to group I (dressing removed on postoperative day one) or group II (dressing removed on postoperative day six). Surgical site infections will be defined by standard criteria from the Centers for Disease Control and Prevention (CDC). Skin colonization will be assessed by culture of samples collected at predefined time points. Patients will score dressing wear time with regard to safety, comfort and convenience.

**Discussion:**

The evidence to support dressing standards for breast surgery wounds is empiric and scarce. CDC recommends protecting, with a sterile dressing for 24 to 48 hours postoperatively, a primarily closed incision, but there is no recommendation to cover this kind of incision beyond 48 hours, or on the appropriate time to shower or bathe with an uncovered incision. The results of the ongoing trial may support standard recommendations regarding dressing wear time after breast reconstruction.

**Trial registration:**

ClinicalTrials.gov identifier:
http://NCT01148823.

## Background

Surgical site infection (SSI) is a relevant problem in surgical practice, with surrounding issues that still need to be clarified
[1-4]. Interventions to reduce the incidence of SSI are essential to reduce not only morbidity, but also costs to the individual and to society
[2,5-7].

The infection risk for clean wounds is estimated to be 1 to 2%
[8]. However, SSI rates following breast surgery seem to be much higher than that expected for clean surgical procedures and range from 1 to 30% in the literature
[7,9-11]. Furthermore, SSI rates after breast cancer surgical procedures are more common than SSI after non-cancer-related breast operations
[7]. The incidence in the literature of SSI after mastectomy varies from 1% to 28%
[5,12-14], and SSI rates after breast reconstructive procedures range from 6.3% to 28%
[5,7,15-18].

Identifying SSI risk factors for breast surgery is essential in order to develop infection-prevention strategies and improve surgical outcomes
[7]. Risk factors for SSI are usually classified into preoperative (patient-related, for example, age, obesity, tobacco use, comorbidities, use of immunosuppressive medications), perioperative (procedure-related factors, such as type and duration of the operation, hypoxia, operating room traffic and operating room parameters) and postoperative categories
[2,19]. One of the major risk factors in the postoperative period is wound management
[2,19-21]. Despite the importance of surgical wound management in preventing infection, literature on incisional wound management is sparse
[21,22].

Postoperative wound care is an ancient practice, with recorded evidence dating back 4,000 years
[23]. Purposes for wound dressing include protection of the wound from trauma and contamination, absorption of wound exudates and compression to minimize edema and obliterate dead space
[23-27].

The search for an ideal postsurgical breast dressing has led to the development of several different materials and application techniques
[28,29]. Despite the abundance of wound dressing products available nowadays, there is little empiric evidence to guide product choice for site-specific incisional wounds
[26,30], and traditional low-technology gauze-based dressings are commonly used
[25,27,29,31,32]. Due to lower costs, this kind of dressing is largely used in the public health system in Brazil.

From the literature, the ideal dressing wear time is also controversial. Some authors recommend the early exposure of the surgical wound, to allow easy wound inspection without inconvenience to the patient, to release the patient for his/her routine personal care and to decrease costs
[21,22,24]. Other authors recommend the use of dressings for a longer time, frequently until sutures are removed, without increase in SSI rates
[6,31,33,34].

The Centers for Disease Control and Prevention (CDC) provide recommendations concerning prevention of SSIs. No recommendation is offered for some practices, either because there is a lack of consensus regarding their efficacy or because the available scientific evidence is insufficient to support their adoption
[19].

Available evidence to support dressing standards for incisional wounds, including breast surgery wounds, is empiric and scarce
[20,23,24,26,27,30,35]. CDC’s guidelines instruct that wounds that are closed primarily should be covered with a sterile dressing for 24 to 48 hours
[19]. There is neither recommendation of the type of dressing nor the ideal dressing wear time following breast surgery. These remain unsolved issues, and decisions regarding routine dressing are made on the basis of surgeons’ personal experience
[19].

This randomized controlled trial was designed to assess the influence of dressing wear time after breast reconstruction on SSI rates, skin colonization and patients’ perceptions of safety, comfort and convenience.

## Methods/Design

### Study aims

To assess whether dressing wear time after breast reconstruction will influence SSI rates. Secondary aims are to assess the influence of dressing wear time on skin colonization and patients’ perceptions with regard to safety, comfort and convenience.

### Ethical issues

The Universidade do Vale do Sapucaí Ethical Committee approved the study protocol (786/07 and 1623/11). Only participants who have agreed to provide written informed consent will be included in the study.

### Study design and setting

This is a two-arm parallel group randomized controlled trial, to be conducted in a university-affiliated hospital. Patients will be recruited from the Breast Unit of the Plastic Surgery Division of the Hospital das Clínicas Samuel Libânio - Universidade do Vale do Sapucaí. This trial was registered in ClinicalTrials.gov (NCT01148823).

### Sample size

SSI rates following breast reconstruction vary in the literature, from 1% a 30%
[1,4,5,9-11]. We considered clinically relevant a 10% difference in SSI rate
[35]. Specifying an acceptable Type 1 error of 5%, and Type 2 error of 20%, the estimated sample size was 100 patients per arm.

### Eligibility criteria

#### Inclusion criteria

Breast cancer patients over 18 years of age undergoing immediate or delayed breast reduction at Hospital das Clinicas Samuel Libânio will be considered eligible for participation.

#### Exclusion criteria

Patients with body mass index (BMI) above 35Kg/m^2^, those with usual contraindications for breast reconstruction procedures, such as diabetes or heavy smoking, will be excluded. Patients whose dressings get wet in the first 24 hours after operation, thus requiring their change, will also be excluded.

### Groups’ assignment, randomization and allocation concealment

Two hundred patients will be prospectively enrolled after giving informed consent. Patients will be randomly assigned to group I (n = 100), which will have dressings removed on the first postoperative day or to group II (n = 100), whose dressings will be removed on the sixth postoperative day. The rationale for comparing 24 hours versus 144 hours of dressing include CDC recommendation of protecting an incision with a sterile dressing for 24 to 48 hours
[19] (group I) and the time of removing sutures (group II).

The allocation will be determined by a computer-generated sequence (Bioestat 5.0, Instituto de Desenvolvimento Sustentável Mamirauá, Belém, PA, Brazil). A numbered and sealed opaque envelope will be opened on the first postoperative day to reveal the group to which the patient is allocated.

### Baseline procedures and interventions

Patients will take a shower with liquid detergent-based chlorhexidine 4% prior to the operation
[36], and an alcoholic solution of chlorhexidine 0.5% will be used for the antisepsis of the surgical site in the operating room
[37]. Patients will undergo immediate or delayed breast reconstruction under general anesthesia, by the use of flaps and/or implants and, performed by the same surgical team. All patients will receive prophylactic antibiotics (cephazolin).

At the end of the operation, the surgical site will be cleansed with sterile physiological saline, a sample for quantitative skin culture will be obtained and a conventional gauze and tape dressing, which use is the established practice in our hospital, will be applied. Sutured wounds will be completely covered with four layers of dry sterile cotton gauze and fixed in place by a microporous adhesive tape. The surgical team will not be aware of the group to which the patient will be allocated.

Patients allocated to group I will be instructed to keep their wounds uncovered and to follow their usual personal hygiene routine, and patients in group II will be instructed not to wet the dressing.

Quantitative skin cultures will be obtained in the operating room immediately before applying the dressing, as well as immediately after the removal of dressing. In group I, an additional sample will be collected at the sixth postoperative day. A standard 5cm by 10 cm area (determined by a sterile pattern) over the surgical wound will be swabbed with a sterile cotton swab pre-moistened with sterile saline. This swab will be placed in a sterile container with 1.0 ml of saline and immediately conducted to the laboratory.

Patients will be discharged from the hospital on the first postoperative day after allocation, and they will return weekly for follow-up, for four weeks.

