### End points

Participation is considered complete after the 30^th^ postoperative assessment day if no implants have been used, or after the 12^th^ postoperative month if an implant was used. Another exit point is if the dressings of group II patients get wet before the sixth postoperative day, thus requiring withdrawal from the study.

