## Discussion

SSI is a major source of adverse events in patients undergoing breast cancer surgical procedures, generating psychological issues, increased duration of hospitalization and costs, as well as delay in commencing postoperative adjuvant therapies
[2,5,11]. Consequently, surgeons should make a determined effort to prevent SSI. As protocols and guidelines should be founded on evidence-based medicine principles, well-designed studies are essential to support or to adjust clinical practice
[20].

Wound management is a key area in preventing SSI
[21]. However, few studies have focused on the management of the wound after closure as a method of reducing infection
[34]. This randomized trial focuses on the influence of dressing wear time in SSI rates. Since the greater the degree of surgical wound contamination, the higher the risk for infection
[2,19], skin colonization assessment is a secondary aim of this study.

The management of surgical wounds should involve the principle of minimizing harm, and patient preference and tolerance must also be considered
[30]. Thus, assessment of patients’ perceptions of dressing wear time is another secondary aim in this trial. Some authors pointed out that omitting a dressing after the first 24 postoperative hours could be convenient for patients, allowing them to carry out their personal hygiene more easily
[24]. However, other authors observed that dressings are comforting to patients by masking their scars without increasing SSI rates
[23,26,35]. Considering the mutilating characteristics of breast cancer treatment, we hypothesize that patients, particularly those who undergo immediate breast reconstruction, might prefer to keep their dressings in place for a longer time, thus delaying the moment of seeing their reconstructed breasts.

CDC’s guidelines for managing surgical wounds that are closed primarily instruct patients to keep their wounds dry and covered for 24 to 48 hours
[19], but the ideal dressing wear time following breast surgery remains an unsolved issue. The results of this trial may support standard recommendations regarding dressing wear time after breast reconstruction.

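### Departures from the assigned wear time end participation in group II only (wet dressing), so the SSI comparison treats the two randomised arms unequally

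*Protocol article*

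**What the plan says.** All places are in the Protocol article.

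- **Allocation and discharge.** Under Groups' assignment, randomization and allocation concealment: "A numbered and sealed opaque envelope will be opened on the first postoperative day". Under Baseline procedures and interventions: "Patients will be discharged from the hospital on the first postoperative day after allocation". The contrast in wear time, day 1 to day 6, therefore plays out at home.
- **Group I after allocation.** "Patients allocated to group I will be instructed to keep their wounds uncovered" (Baseline procedures and interventions). No consequence is attached to covering the wound again.
- **Group II after allocation.** Patients are told to keep the dressing dry. End points adds: "Another exit point is if the dressings of group II patients get wet before the sixth postoperative day". The sentence goes on to require withdrawal from the study.
- **Wet dressings before allocation.** Exclusion criteria: "Patients whose dressings get wet in the first 24 hours after operation, thus requiring their change, will also be excluded". This applies to everyone and falls essentially before the envelope is opened, so it is not an arm-specific rule.
- **Contacts.** A culture is taken when the dressing comes off, on day 1 in group I and day 6 in group II. In addition: "In group I, an additional sample will be collected at the sixth postoperative day". Follow-up visits are weekly.
- **Preference.** The Discussion hypothesises that patients, particularly after immediate reconstruction, "might prefer to keep their dressings in place for a longer time, thus delaying the moment of seeing their reconstructed breasts".

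**The concern.** Randomisation makes the arms comparable only while every allocated patient stays in the comparison. Here a post-allocation event that can occur in one arm only removes patients from that arm. A group I patient who covers the wound again stays in, and so does one who would have wetted a dressing had one been assigned. A group II patient whose dressing gets wet leaves, and her later SSI status is lost.

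Wetting is also part of what a six-day dressing entails in practice. Taking those patients out of group II removes part of the effect of the longer wear time, and the bias can run either way depending on their infection risk.

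A second, smaller matter concerns interpretation. If some group I wounds are covered again, or some group II dressings come off early and dry, the arms move closer in actual exposure. The article describes nothing that would show this between discharge and day 6. A result of no difference would then be harder to read, and the Discussion hopes the results will support a standard recommendation on wear time.

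**Working it through.** **1. The rules side by side**

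| Departure between day 1 and day 6 | Arm | Stated consequence | Seen at the day-6 contact? |
|---|---|---|---|
| Dressing gets wet | II | Withdrawal | Not applicable, patient has left |
| Dressing removed early, dry | II | None stated | Absence visible, timing not |
| Dressing replaced | II | None stated | Not reliably |
| Wound covered again | I | None stated | Only if still covered that day |

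Only the first row has a consequence, and it exists in one arm.

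**2. The planned sample size**

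Inputs from Sample size: a 10% difference in SSI rate (read as 10 points), type 1 error 5%, type 2 error 20%, 100 per arm. The base rate and sidedness are not given; the cited range is 1% to 30%. With 2% v 12%, two-sided (1.96 and 0.842 are the normal quantiles):

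- Pooled: n = [1.96·√(2·0.07·0.93) + 0.842·√(0.02·0.98 + 0.12·0.88)]² / 0.10², which rounds up to 102.
- Unpooled: n = (1.96 + 0.842)²·(0.0196 + 0.1056) / 0.10², which rounds up to 99.

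So 2% v 12% is one pair that fits 100 per arm. 5% v 15% does not (141 pooled). I use 2% v 12% below as an assumption.

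**3. What withdrawal can do to the group II rate**

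Let p be the SSI risk in all of group II, w the share withdrawn for wetting, and q the risk in that share. The rate among those left is (p − w·q)/(1 − w). Only the relevance threshold comes from the article; w and q are assumptions. With p = 12%:

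- w = 10%, q = 12%: (0.12 − 0.012)/0.90 = 12.0%, no shift.
- w = 10%, q = 24%: (0.12 − 0.024)/0.90 = 10.7%, shift −1.3 points.
- w = 10%, q = 36%: (0.12 − 0.036)/0.90 = 9.3%, shift −2.7 points.
- w = 20%, q = 24%: (0.12 − 0.048)/0.80 = 9.0%, shift −3.0 points.
- w = 10%, q = 6%: (0.12 − 0.006)/0.90 = 12.7%, shift +0.7 points.

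The shift is zero only if wetting is unrelated to infection risk, which the design cannot show once those patients have left.

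**4. What re-covering could do to power (illustration only)**

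If a share r of group I covers the wound again and takes on the group II risk, the difference becomes 10·(1 − r) points: 8 at r = 20%, 7 at r = 30%. Exact power of the two-sided Fisher test, 100 per arm:

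| Base pair | r | Group I lower-risk | Group I higher-risk |
|---|---|---|---|
| 2% v 12% | 0 | 76.2% | 76.2% |
| 2% v 12% | 20% | 46.5% (4% v 12%) | 58.7% (2% v 10%) |
| 2% v 12% | 30% | 33.8% (5% v 12%) | 48.2% (2% v 9%) |
| 5% v 15% | 0 | 58.6% | 58.6% |
| 5% v 15% | 20% | 36.1% (7% v 15%) | 42.0% (5% v 13%) |
| 5% v 15% | 30% | 27.0% (8% v 15%) | 33.8% (5% v 12%) |

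The re-covering share, the base rate and the direction are all assumed. At 5% v 15% the shortfall from 80% is already there at r = 0, so it belongs to the sample size and not to adherence.

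**The case against.** The strongest reply has four parts.

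- **This is a condensed article.** Visit forms are normally left to the full protocol, which may hold an adherence item. That stands for the missing record of cover at home, which is therefore only a suggestion. It does not touch the withdrawal rule, which the article states.
- **The asymmetry follows from the intervention.** After day 1 only group II has a trial dressing that can get wet. That explains how the rule arose. It is also why the rule harms the comparison: the event that removes patients depends on the arm.
- **Comparing patients as instructed is a relevant practical question.** Agreed. That comparison needs every patient kept in the allocated arm, including those whose dressing got wet.
- **Much of the exposure is observed.** Removal on day 1 in group I is tied to a culture, and both arms are swabbed around day 6, when a wound still covered or a dressing already gone would be seen. This also stands.

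Two stronger readings are tempting. A reader might infer that actual wear time is unknown in both arms. The cultures at removal and on day 6 contradict that; what goes undescribed is transient covering in group I, and replacement or the time of early removal in group II. A reader might also infer that the protocol expects group I to cross over. The Discussion says only that patients "might prefer to keep their dressings in place for a longer time". That is a hypothesis about preference, in support of a preference outcome, and the same paragraph reports the opposite view that going without a dressing may be convenient.

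**Conclusion.** The point holds for the stated rule. A wet dressing ends participation in group II, while no departure in group I has any consequence, so the arms are handled unequally after randomisation. The article gives no wetting frequency, so the size of the bias cannot be computed. Under the assumptions above it runs from nil to about 3 points against a relevant difference of 10, in either direction.

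The missing record of cover between discharge and day 6 is a minor matter of interpretation. It invalidates no planned test. The power figures show how sensitive the result would be to re-covering; they do not show that re-covering occurs, and should not be cited as the trial's expected power.

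**What to change.** 1. **Reconcile End points with the allocation and intervention sections.** State that every randomised patient is followed for SSI to day 30, or to 12 months with an implant, and analysed in the allocated arm whatever happens by way of wetting, re-covering or early removal. How a wet dressing is managed clinically is a separate matter on which nothing is proposed here. For group II patients already withdrawn, recover SSI status where records and consent allow. The cost is a change of text and continued weekly visits for a few patients; some outcomes already lost may not be recoverable.
2. **At the existing day-6 contact, record cover in both arms.** Ask whether and for how long the wound was covered since day 1 and, in group II, whether the dressing is the original one. Report this by arm and use it to qualify a null result, not as a condition for drawing one. The cost is two items on a form and one table, with no new visit. The data are self-reported and, with 134 of 200 patients operated on by the end of December 2012, available for at most about 200 − 134 = 66.

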### Microbiological methods

Standard microbiological methods and criteria will be used to identify microorganisms
[38]. Aliquots of 0.2 ml of the sample will be plated on hypertonic manitol (HM) agar, selective for staphylococci; on blood agar, to identify hemolytic colonies; on Sabouraud agar with chloramphenicol (0.05mg/ml), selective for fungi and yeasts; and on eosin-methylene blue (EMB) agar, selective for enterobacteria. The plates will be incubated aerobically for 48 hours at 37°C. The same laboratory technician will process all samples and, after 48 hours, the plates will be examined by a microbiologist.

Bacterial count results will be reported as colony forming units (CFU) per plate. Whenever CFU count in a plate exceeds 300, it will be scored as over 300. Staphylococci will be identified as coagulase-negative *Staphylococcus* sp. or *S. aureus* on the basis of Gram stain, the presence of hemolysis and on coagulase testing. The same microbiologist will assess all the plates. Both the laboratory technician and the microbiologist will be blinded.

### Assessment of postoperative infection

The Centers for Disease Control and Prevention (CDC) considers SSI to be an infection that occurs within 30 days after the operative procedure if no implant is left in place, or within one year if an implant is in place and the infection appears to be related to the operative procedure
[39]. Thus, patients will be systematically followed-up once a week for 30 days regarding postoperative infection, by a single surgeon. Patients who receive an implant will have an additional assessment by the same surgeon, one year after the operation. The CDC definitions and classifications of SSI will be considered (Table 
1)
[39]. As with all CDC definitions of nosocomial infections, a surgeon’s diagnosis of infection will be considered an acceptable criterion for an SSI
[39].

**Table 1 T1:** **CDC definitions of SSI**[39]

**Superficial incisional SSI**	**Deep incisional SSI**	**Organ/Space SSI**
Involves only skin or subcutaneous tissue and meets at least one of the following:	Involves deep soft tissues (fascial and muscle layers) and meets at least one of the following:	Involves any part of the anatomy (organs or spaces) and meets at least one of the following:
• Purulent drainage from the superficial incision;	• Purulent drainage from the deep incision but not from the organ/space component of the surgical site;	• Purulent drainage from a drain that is placed through a stab wound into the organ/space;
• Organisms isolated from an aseptically obtained culture of fluid or tissue from the superficial incision;	• A deep incision that spontaneously dehisces or is deliberately opened by a surgeon when the patient has at least one of the following signs or symptoms: fever (>38°C), localized pain or tenderness, unless the incision is culture-negative;	• Organisms isolated from an aseptically obtained culture of fluid or tissue in the organ/space;
• At least one of the following signs or symptoms of infection: pain or tenderness, localized swelling, redness or heat, and the superficial incision is deliberately opened by surgeon unless the incision is culture-negative;	• An abscess or other evidence of infection involving the deep incision is found on direct examination, during reoperation, or by histopathologic or radiologic examination;	• An abscess or other evidence of infection involving the organ/space that is found on direct examination, during reoperation, or by histopathologic or radiologic examination;
• Diagnosis of superficial incisional SSI by the surgeon or attending physician.	• Diagnosis of deep incisional SSI by the surgeon or attending physician.	• Diagnosis of an organ/space SSI by the surgeon or attending physician.

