### Outcomes measures

The primary outcome is the incidence of SSI, which will be defined on the basis of CDC’s definitions
[39]. Skin colonization rates and patients’ preferences regarding dressing wear time are secondary outcomes.

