### Statistical analysis

The rejection level for the null hypothesis will be fixed at 5% (α ≤ 0.05). The Mann-Whitney test will be used to compare groups I and II with regard to age, BMI and duration of operation.

The Fisher test will be used to compare groups I and II regarding SSI occurrence. Logistic regressions will be applied to detect significant associations between variables such as age, BMI and duration of operation and the incidence of SSI.

For inter-group assessment of skin colonization, the Mann-Whitney test will be used to compare groups I and II pre-dressing and at the sixth postoperative day. These tests will be applied independently for each medium used. Because skin colonization could play a role in SSI rates, an intra-group assessment of skin colonization will also be performed. For this assessment, in group I Friedman two-way analysis of variance will be used to assess the differences in number of CFU among the three moments (pre-dressing, first and sixth postoperative day). Whenever the difference is significant, the Friedman two-way analysis of variance will be complemented by the multiple comparisons test to determine which moment significantly differed from the others. In group II, the Wilcoxon test will be used to compare the number of CFU pre-dressing and at the sixth postoperative day.

The Kolgomorov-Smirnov test will be applied to compare the two groups regarding patients’ assessments of safety, comfort and convenience. The Fisher test will be used to compare groups I and II regarding patients’ choice (one day or six days).

Statistical analysis will be performed using SPSS (Statistical Package for Social Sciences, Inc., Chicago, IL, USA) v.18 and Bioestat 5.0 (Instituto de Desenvolvimento Sustentável Mamirauá, Belém, PA, Brazil).

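### The primary SSI outcome pools a 30-day window (no implant) with a one-year window (implant), which mixes length of observation into the risk-factor regressions and may cost power in the arm comparison

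*Protocol article*

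**What the plan says.** Under Assessment of postoperative infection, the article adopts the CDC rule. For most patients SSI means "an infection that occurs within 30 days after the operative procedure if no implant is left in place". A longer period applies to the others: "within one year if an implant is in place and the infection appears to be related to the operative procedure". Everyone is seen alike in the first month: "patients will be systematically followed-up once a week for 30 days regarding postoperative infection, by a single surgeon". After that only some are seen again: "Patients who receive an implant will have an additional assessment by the same surgeon, one year after the operation".

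End points follows the same split. Participation closes at day 30 without an implant, "or after the 12^th^ postoperative month if an implant was used". Outcomes measures makes this the single primary outcome and sets no common time point: "The primary outcome is the incidence of SSI, which will be defined on the basis of CDC’s definitions".

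Baseline procedures and interventions enrols flap and implant reconstructions together and gives no expected mix. Statistical analysis compares SSI between arms with a plain Fisher test and adds: "Logistic regressions will be applied to detect significant associations between variables such as age, BMI and duration of operation and the incidence of SSI". Neither implant status nor length of follow-up is named there.

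**The concern.** The exposure under test ends on postoperative day 1 or day 6, and no later difference in care between the arms is described. For some patients the outcome closes at day 30. For others it runs about eleven months longer, and that stretch rests on one visit. The resulting proportion is neither a 30-day nor a one-year risk, and its level depends on how many patients receive implants.

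Two things are at stake:

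- **Arm comparison.** Late infections that have nothing to do with the dressing would add events to both arms and reduce power.
- **Risk-factor regressions.** Implant patients have roughly twelve times as long in which to record an SSI. A covariate that differs between implant and flap operations would partly measure that extra time.

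**Working it through.** **Inputs from the article.** 100 patients per arm; a 10% difference in SSI rate, read as 10 percentage points; type 1 error 5%; type 2 error 20%; the two windows above.

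**Inputs not in the article, so assumed.** 30-day SSI risk p in each arm; implant share s; late risk L (day 31 to one year) among implant patients free of early SSI; operation times by type of reconstruction.

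**The plan's own figure.** Sample size fixes no base rate, only a literature range of 1% to 30%, so 100 per arm cannot be reproduced uniquely. The two-sided formula with pooled variance and no continuity correction gives 102 per arm at 2% v 12%, 141 at 5% v 15% and 199 at 10% v 20%. The illustration below uses 5% v 15%, with 2% v 12% as a check.

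**Step 1: late infections independent of arm.** The pooled risk in an arm is q = p + (1 − p)·s·L. With s = 0.50 and L = 0.06, s·L = 0.03, so

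- 0.05 + 0.95 × 0.03 = 0.0785
- 0.15 + 0.85 × 0.03 = 0.1755

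The difference moves from 10.0 to 9.7 points, and the risk ratio from 3.0 to 2.24. Exact two-sided Fisher power at 100 per arm:

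| Implant share | Late risk | Pooled risks | Difference (points) | Power |
|---|---|---|---|---|
| 30-day SSI only | – | 5.0% v 15.0% | 10.0 | 58.6% |
| 25% | 1% | 5.2% v 15.2% | 9.98 | 57.4% |
| 25% | 3% | 5.7% v 15.6% | 9.93 | 55.2% |
| 50% | 6% | 7.9% v 17.6% | 9.70 | 47.1% |
| 75% | 10% | 12.1% v 21.4% | 9.25 | 35.4% |

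At 2% v 12%, power falls from 76.2% to 65.3% (50% implants, 3% late) and 56.4% (50%, 6%). The loss is not peculiar to the 5% v 15% scenario.

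**Step 2: late infections that share the dressing effect.** Keep s = 0.50 and an average late risk of 6%, with a relative risk between arms.

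- Relative risk 2: late risks 4% and 8%. Pooled risks are 0.05 + 0.95 × 0.5 × 0.04 = 0.069 and 0.15 + 0.85 × 0.5 × 0.08 = 0.184. Power is 63.2%.
- Relative risk 3, the same as for early infection: late risks 3% and 9%. Pooled risks are 0.064 and 0.188. Power is 70.8%.

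Both exceed 58.6%, so the sign of the power effect depends on an unknown.

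**Step 3: what the window alone does to an implant comparison.** Suppose 30-day risk is 5% with or without an implant. With L = 0.05, implant patients reach 0.05 + 0.95 × 0.05 = 0.0975. The odds ratio is (0.0975/0.9025) ÷ (0.05/0.95) = 2.05, with no difference in 30-day risk. At L = 2% and 10% it is 1.41 and 3.22. At a 30-day risk of 10%, the three values are 1.20, 1.53 and 2.11.

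**Step 4: carry-over to duration of operation.** Large-sample simulation, assuming half implants, mean 2.5 h (implant) v 4.5 h (flap), 10% SSI at 3.5 h, and a within-type SD of 0.75 or 1.0 h. Estimated odds ratio per hour at L = 3%, 6% and 10%:

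| True value | SD 0.75 h | SD 1.0 h | SD 1.0 h, implant status added |
|---|---|---|---|
| 1.25 | 1.12, 1.03, 0.93 | 1.14, 1.06, 0.98 | 1.22, 1.19, 1.17 |
| 1.00 | 0.92, 0.86, 0.79 | 0.94, 0.89, 0.84 | 1.00-1.01 throughout |

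If operation times do not differ by implant use, there is no false association and no reversal. Adding implant status removes the false association but leaves some attenuation of a true one, because late events do not follow the early-risk model.

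**The case against.** The dual window is the cited CDC definition. It was adopted on purpose, and the follow-up and end points match it, so there is no contradiction. This stands.

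A reader might infer that late implant infections are unrelated to a one- or six-day dressing and therefore dilute the comparison. The article does not support that. It counts a late infection only if it appears related to the operation. Its Discussion links wound contamination to infection risk, and early contamination could surface late on an implant. Step 2 shows that power then rises.

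A reader might also infer bias between arms. Implant use is settled at surgery, and the envelope is opened on the first postoperative day, with the surgical team unaware of allocation until then. The windows are balanced in expectation and the type 1 error of the Fisher test holds. Even with arm-neutral late events, the absolute difference, the scale on which the target is set, shrinks only to between 9.98 and 9.25 points.

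On the regressions, the covariate list is open-ended and a fuller plan, not shown, could include implant status. The operation times in Step 4 are assumed. So distortion is a risk of the analysis as written, not an established result. These regressions also do not test dressing wear time.

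Loss of implant patients between day 30 and month 12 is conjecture, and its handling can properly sit in an analysis plan. It forms no part of this point.

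**Conclusion.** The point holds in a limited form. One primary outcome combines two unequal risk windows, and the stated analyses take no account of which window a patient had.

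For the arm comparison this is a question of power and interpretation, not validity. If late infections are independent of wear time, power at 5% v 15% falls from 59% to between 57% and 35% over the assumed 25-75% implants and 1-10% late infection. If they share the dressing effect, power rises. The article gives neither the implant share nor a late-infection rate, so the direction and size cannot be settled from it.

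The firmer part is the regressions. As written, they compare patients observed for 30 days with patients observed for a year. Any covariate linked to implant use takes on part of that difference. Under the assumed durations, a null odds ratio of 1.00 per hour is estimated at about 0.94 to 0.79. Whether a true association would be reversed, rather than weakened, depends on the spread of operation times and on a late-infection rate near 10%.

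**What to change.** - Run the logistic regressions on CDC-defined SSI within 30 days in every patient. If the pooled outcome is kept, include implant status as a covariate.
- Prespecify the between-arm Fisher comparison of 30-day SSI in all patients, preferably as the primary analysis.
- Report SSI from day 31 to one year as a separate outcome, compared between arms within the implant subgroup.
- Keep the one-year visit.

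The cost is wording in the outcome and analysis sections, settled before any unblinded analysis. Thirty-day status is already collected for everyone, so no visit or patient is added. The downside is that late implant infections leave the 30-day analysis, which loses some signal if wear time does affect them. It also departs from the full CDC definition for implant patients; the separate one-year outcome keeps that information.
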